## **1.6. Rationale for the study**

The purpose of this trial is to prospectively assess the utility of blood-based next generation sequencing to accelerate time to treatment for newly diagnosed patients with advanced NSCLC, compared to conventional molecular tumour testing.

Many other studies [14,17, 21-25] have already demonstrated that plasma-based NGS genotyping is feasible, rapid and useful in the clinical practice setting for patients with advanced NSCLC.

Plasma NGS used in patients with newly diagnosed advanced NSCLC successfully identifies guideline recommended biomarkers at a rate at least as high as SOC tissue testing and returns these results significantly faster and for a significantly higher proportion of the population. Moreover, ctDNA-detected guideline recommended biomarkers were invariably present in tissue, when tissue was successfully tested, reinforcing that ctDNA genotyping results may be used in clinical management in the same way tissue genotyping results are currently used [9, 14]

These results suggest that initial biomarker assessment using ctDNA rather than tissue (“blood-first”), reserving tissue for PD-L1 IHC and reflex testing when ctDNA is negative for any known oncogenic driver mutations, will improve the biomarker discovery rate, turn-around time and decrease time to treatment. The net result will be to increase the number of patients with newly diagnosed advanced NSCLC that will receive guideline complete biomarker testing and be able to access a precision medicine approach to their cancer therapy [14]. The acceleration of time to diagnosis and treatment is expected to favorably impact outcomes in this population.

Based on these promising results, in this study we will analyze if the “blood-first” approach can accelerate time to treatment compared with the standard diagnostic pathway including tissue genotyping.

## **2. STUDY OBJECTIVES**

This study will assess the utility of liquid biopsy to accelerate time to treatment for selected patients with radiographic evidence of advanced lung cancer (Figure 1).

### **2.1. Primary Objective**

1. To compare time to treatment initiation in advanced NSCLC patients for those that had a liquid biopsy compared to patients referred in the previous 12 months that meet the eligibility criteria.

Hypothesis: Wait times to treatment initiation will be reduced up to 50% (4-6 weeks) for patients who have a liquid biopsy with actionable lung cancer targets.

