104 missed treatment opportunities. For example, because of delays in receiving molecular test  
105 results, 19% of patients that could have accessed targeted therapy proceed with  
106 chemotherapy instead, and another 13% require repeat biopsies, which further delays time to  
107 treatment start [11]. Further, many advanced NSCLC patients are not well enough to undergo  
108 a repeat biopsy, nor are many well enough to wait for delayed results.

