### 109 1.2. *Wait Times in NSCLC*

110 For advanced non-small cell lung cancer (NSCLC) patients, clinical outcomes are directly  
111 impacted by time from symptom onset to initiation of appropriate treatment. Unfortunately, for  
112 most lung cancer patients, the cancer journey is drawn out with many delays until diagnosis  
113 and treatment. The time from the initiation of referral to a cancer centre until treatment can  
114 take more than 12 weeks for patients with advanced NSCLC (Figure 1) [12]. This includes  
115 waiting for diagnostic tests such as imaging, biopsy, pathology, immunohistochemistry and  
116 genomic testing, as well as clinical assessment. Despite rapid diagnostic programs that have  
117 been designed to address these issues, limited resources including biopsy bookings,  
118 pathology and testing delays remain challenging. Further, these delays are exacerbated by  
119 the recent COVID-19 pandemic that has impacted all aspects of healthcare delivery.

Time to diagnosis can vary widely, as this is a complex and multi-dimensional variable. We have learned that prolonged time from symptoms to treatment decision significantly reduces the chance for a patient to access precision medicine, and in some cases, any treatment. The “wait time” to treatment from the patient’s point of view is a period of uncertainty that feeds fear and anxiety [13]. It also has a detrimental impact on patient outcomes, with fewer patients able to access effective therapy and consequently reduced survival.

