### 292 **3.2. Data Collection**

293 Molecular profiling results from both tumour and ctDNA will be recorded, and incremental  
294 actionable genomic targets will be identified for each method. Any complications from either  
295 the liquid or tumour biopsy will be captured, as well as any failure of tissue or blood sampling,  
296 molecular profiling and repeat biopsies.

297 Turnaround time for molecular results for liquid and tumour tissue biopsy, time to treatment  
298 initiation, treatment received and outcomes including tumour response, progression-free and  
299 overall survival will be collected.

300 Patients will be asked to complete the EQ-5D-5L at baseline and at 3 months to assess  
301 quality of life. Patients may complete the EQ-5D-5L survey by phone or by mail if they do not  
302 have a routine (in person) doctor's visit scheduled. Patients that are unable to complete the  
303 EQ-5D-5L (literacy, physical issues, unavailable translation) are still eligible to participate.

304 Patient visits and procedures during the diagnostic work up will be collected. Costs of both  
305 diagnostic strategies will be captured using time in motion studies, direct costs from UHN and  
306 list costs as appropriate. These will be presented as a cost-consequence analysis of liquid  
307 biopsy vs. standard of care tissue biopsy and molecular profiling.

308

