371  Baseline quality of life assessment should be completed prior to the blood draw when  
372 possible.

373

374 **6. STUDY DESIGN, STATISTICAL ANALYSIS, SAMPLE SIZE CALCULATION, AND**  
375 **ACCRUAL PROJECTIONS**

376 **6.1. Study Design**

377 This is a single arm, minimally invasive non-therapeutic study conducted at a single centre.

378 The time to treatment decision ( $T_{LB}$ ) in the study cohort by liquid ( $T_L$ ) and tissue biopsy ( $T_B$ ) is  
379 measured from the date of referral to the earliest date of receiving a liquid or tissue biopsy  
380 report indicating actionable genomic aberrations, or  $T_{LB} = \min(T_L, T_B)$ . The time to treatment  
381 decision using tissue biopsy alone ( $T_B$ ) will be collected in a chart-review comparison cohort  
382 (patients referred in the previous 12 months that meet the eligibility criteria). The time to  
383 treatment decision by liquid biopsy ( $T_{LB}$ ) vs by tissue biopsy alone ( $T_B$ ) will be compared.

384 **6.2. Statistical Analyses**

385 The primary objective is to compare time to treatment initiation in advanced NSCLC patients  
386 for those that had a liquid biopsy compared to patients referred in the previous 12 months that  
387 meet the eligibility criteria. Time from referral to systemic treatment decision, by tissue biopsy  
388 alone vs by liquid and tissue biopsy, will be compared using a two-sample t-test or a Wilcoxon  
389 Mann-Whitney test if the normality assumption cannot be satisfied.

390

The secondary objectives are:

- To compare time to treatment initiation in a subgroup of patients with advanced non-squamous NSCLC with a smoking history of  $\leq 15$  pack years;
- To evaluate result turnaround time of liquid biopsy compared to standard of care tissue biopsy and testing from time of Lung RAMP referral within the study cohort using a paired t-test or Wilcoxon signed rank test;
- To evaluate concordance between liquid and tissue for identification of actionable targets within the study cohort; and,
- To model cost-effectiveness of upfront use of liquid biopsy to triage advanced NSCLC to medical oncology compared to current standard of care costs.

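### The primary endpoint has two different stop events, and they score a driver-positive patient who starts chemotherapy before a late report in opposite ways

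*Protocol*

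**What the plan says.** The protocol describes the primary outcome in two ways.

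- **Treatment initiation.** Section 2.1: "To compare time to treatment initiation in advanced NSCLC patients for those that had a liquid biopsy compared to patients referred in the previous 12" (the unit is months). The hypothesis beneath it reads "Wait times to treatment initiation will be reduced up to 50% (4-6 weeks) for patients who have a liquid biopsy with actionable lung cancer targets". The opening sentence of section 6.2 repeats this objective. The legend to Figure 5 defines the difference being powered as time from referral to treatment, in weeks.
- **Treatment decision.** Section 6.1 defines a time "measured from the date of referral to the earliest date of receiving a liquid or tissue biopsy", where what counts is a "report indicating actionable genomic aberrations", with T_LB = min(T_L, T_B) in the study cohort and T_B alone in the chart-review cohort. The test sentence of section 6.2 then names the variable to be compared: "Time from referral to systemic treatment decision, by tissue biopsy" alone versus liquid and tissue biopsy together.

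No section says which treatment counts as initiation. The word systemic appears only in section 6.2.

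The background explains why this matters. Section 1.1 reports that, because results are late, "19% of patients that could have accessed targeted therapy proceed with" chemotherapy instead. Section 1.2 says that outcomes are "impacted by time from symptom onset to initiation of appropriate treatment". Section 3.2 collects time to treatment "initiation, treatment received and outcomes including tumour response, progression-free and" overall survival, but no section uses the treatment received to define the primary event. Section 6.2 treats it descriptively. For the chart-review cohort, section 6.1 names only T_B.

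**The concern.** A treatment start and a report date are different events, and for one group of patients they fall in the reverse of the intended order. Someone with an actionable aberration who begins chemotherapy before the tissue report arrives has a treatment date ahead of the so-called decision date. These are the patients the hypothesis is about, and the protocol names their situation as a harm of the current pathway.

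On the initiation clock, that harm enters the comparison cohort as a short wait and makes liquid biopsy look less useful than it is. On the report clock, the same patient contributes a long wait, but the date no longer marks when treatment was chosen. Neither clock records whether the drug started was the one the genotype indicated, and no planned between-cohort comparison does so. The result could therefore depend on which section the analyst and the chart abstractor follow.

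**Working it through.** **1. The two clocks for one patient.** Let a driver-positive comparison patient start chemotherapy c weeks after referral and receive the tissue report at r weeks, with r > c.

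| Source | Stop event | Recorded time |
|---|---|---|
| 2.1, first sentence of 6.2, Figure 5 | treatment starts | c (short) |
| 6.1, test sentence of 6.2 | report of an actionable aberration | r (long) |

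The two readings differ by r − c for the same patient.

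**2. The plan's own power (section 6.3).** Inputs: N1 = N2 = 24, SDs 4 and 5 weeks, two-sided alpha 0.05, unequal-variance t-test.

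- SE = √(16/24 + 25/24) = √1.708 = 1.307 weeks
- Satterthwaite df = 43.9; critical t = 2.016
- Noncentrality = difference / 1.307

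Power is 84.9%, 96.3% and 99.4% for 4, 5 and 6 weeks, against the stated 85%, 96% and 99%. The plan's figures reproduce.

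**3. Attenuation on the initiation clock (illustration).** Let a share f of comparison patients stop the clock g weeks before matched therapy would have started. The comparison mean falls by f × g, and the observed difference is d − f × g.

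- f = 0.19, the background figure in section 1.1.
- g = 2 to 4 weeks, an assumption. The documents give no such gap; section 1.4 gives a pre-pandemic mean of 28 days from biopsy to molecular result.
- No chemotherapy-first patients in the liquid-biopsy group, and SDs unchanged. Both are assumptions.

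Loss: 0.19 × 2 = 0.38 weeks; 0.19 × 4 = 0.76 weeks.

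| True gain | Power, no loss | g = 2: gain seen, power | g = 4: gain seen, power |
|---|---|---|---|
| 4 weeks | 84.9% | 3.62, 77.3% | 3.24, 67.9% |
| 5 weeks | 96.3% | 4.62, 93.3% | 4.24, 88.7% |
| 6 weeks | 99.4% | 5.62, 98.8% | 5.24, 97.5% |

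**4. Sensitivity.**

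- Section 6.3 expects 25 to 50 comparison patients. With 24 v 50, power at a true 4 weeks is 95.3% without loss, 90.9% at g = 2 and 83.8% at g = 4.
- Letting the comparison variance grow by f(1 − f)g² changes the 24 v 24 figures at 4 weeks only to 76.7% and 65.3%.
- Longer gaps of 6 and 8 weeks would give 57% and 46% at a true 4 weeks, and 95% and 92% at 6 weeks.

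**5. Could the effect reverse?** The observed gain reaches zero when f × g = d. With f = 0.19 and d = 4, that needs g = 4/0.19 ≈ 21 weeks. Section 1.4 puts the whole wait at about 3 months, or potentially longer during the pandemic.

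**The case against.** The strongest reply is that section 6.1 is the only operational definition in the protocol. Under it a chemotherapy start does not stop the clock, so the patient keeps a long time. That is correct. A reader might infer from section 2.1 that any treatment ends the interval and that chemotherapy given for want of a result is therefore scored as a success. The protocol never says any treatment; it leaves the qualifying treatment open, and 6.1 points the other way. But 6.1 does not settle the matter either, because the objective, the recorded item in section 5.4 and the power basis all remain treatment initiation.

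Other stronger readings also lack support:

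- **The endpoint runs in the wrong direction.** The arithmetic shows a smaller gain, not a loss. The bias is against liquid biopsy, so it creates no false claim of benefit.
- **Palliative radiotherapy would stop the clock.** Section 6.2, the analysis section, says systemic.
- **The trial is underpowered for this reason.** The fall below 80% occurs only at a true 4 weeks with 24 v 24. That calculation belongs to the subgroup with at most 15 pack-years, a secondary objective, and does not measure power for the primary comparison.

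It is also fair to say that a matched-therapy measure answers a different question from the primary objective and that its detail could sit in a SAP. Hence it is proposed below only as supportive. The conflict between stop events is not a matter of SAP detail, because the protocol itself states both.

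**Conclusion.** The point holds as an inconsistency in the primary endpoint. The protocol fixes two stop events, leaves the qualifying treatment unspecified, and so classifies one clinically important group in opposite ways; neither version shows receipt of matched therapy.

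The size is moderate. If initiation is used, the apparent gain shrinks by about 0.4 to 0.8 weeks. That matters at the low end of the hypothesised 4 to 6 weeks and little at the high end. This rests on a background 19% that is not an estimate for this comparison cohort, an assumed 2 to 4 week gap, and no chemotherapy-first patients in the study cohort; any there would reduce the bias. The inconsistency itself needs none of these assumptions.

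**What to change.** Reconcile sections 2.1, 6.1, 6.2 and Figure 5 to one primary stop event, the date of first systemic therapy, measured from referral and applied identically to the study and chart-review cohorts. Report the section 6.1 report-date time separately as turnaround.

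For patients with an actionable aberration found by any test, add a supportive, not co-primary, between-cohort analysis of two items:

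- the proportion whose first systemic therapy was genotype-matched;
- the time to matched therapy, with unmatched systemic therapy first as a competing event.

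This changes measurement only, not care. The cost is wording plus one more date and drug class abstracted per comparison chart; treatment received is already collected in the study cohort. The limitation is that matched therapy is defined only for the minority with an actionable aberration. Section 6.3 gives 28.2% of non-squamous patients for its four listed genes, though 59% in the light and never smokers.

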### **2.2. Secondary Objectives**

1. To compare time to treatment initiation in a subgroup of patients with advanced non-squamous NSCLC with a smoking history of  $\leq 15$  pack years.

250

251 2. To evaluate result turnaround time of liquid biopsy compared to standard of care tissue  
252 biopsy and testing from time of Lung RAMP referral.

253 Hypothesis: Molecular results from liquid biopsy will be faster than standard of care  
254 tissue profiling.

255 3. To evaluate concordance between liquid and tissue for identification of actionable  
256 targets.

257 Hypothesis: We hypothesize that liquid and tissue molecular results will be comparable  
258 assuming use of broad based NGS panel testing for both.

259 4. To model cost-effectiveness of upfront use of liquid biopsy to triage advanced NSCLC  
260 to medical oncology compared to current standard of care costs.

261 Hypothesis: Upfront liquid biopsy will save biopsy costs in a subset of patients,  
262 compared to similar profiling in tumour tissue.

### 263 **2.3. Exploratory Objectives**

264 1. To model the impact of using liquid biopsy ("blood-first") to permit diagnostic cancer  
265 tissue sparing.

266 2. To explore treatment outcomes using liquid biopsy including response and  
267 progression-free survival with targeted therapy.

268

## 269 **3. METHODS**

270 This is a prospective single arm, non-therapeutic, minimally invasive study which will  
271 conducted at the University Health Network (UHN). One hundred and fifty patients will be  
272 accrued over an estimated 12-18 months. Based on current Lung RAMP referral patterns and  
273 demographics, one third will be never smokers (target subgroup accrual N=40).

274 Eligible patients will be identified through the weekly Lung RAMP MCC and contacted by the  
275 study coordinator. Consenting patients would undergo liquid biopsy (plasma ctDNA testing) in  
276 addition to standard of care imaging, tumour biopsy and tumour tissue molecular profiling  
277 through Lung RAMP. Patients with non-diagnostic tumour biopsies or insufficient tumour  
278 tissue for molecular profiling would also be eligible to participate.

279 Consenting patients would undergo liquid biopsy during their first or next onsite visit to UHN  
280 (e.g. imaging, standard of care blood tests or medical assessment). Whenever possible, the  
281 liquid biopsy would be added to a planned blood draw for standard of care, avoiding  
282 additional venipuncture for the patient. A total of 4 Streck tubes of blood (40 mL total) will be  
283 drawn. Samples will be de-identified and labelled with a study code.

### 284 **3.1. Liquid Biopsy**

285 Consenting patients will undergo peripheral blood draw (approximately 40 mL) collected in  
286 Streck™ tubes or kits provided by Inivata. Two tubes (20 mL) will be shipped to Inivata (North  
287 Carolina, USA) for InVisionFirst® Lung profiling in real time. The remaining 2 tubes will be  
288 sent to the Advanced Molecular Diagnostics Laboratory (AMD) at Princess Margaret Cancer  
289 Centre for nucleic acid extraction and mutation profiling using the Oncomine™ Pan-Cancer

290 Cell-Free Assay (ThermoFisher). This panel can detect lung tumour-derived clinically-relevant  
291 SNVs, small indels and fusions.

### 292 **3.2. Data Collection**

293 Molecular profiling results from both tumour and ctDNA will be recorded, and incremental  
294 actionable genomic targets will be identified for each method. Any complications from either  
295 the liquid or tumour biopsy will be captured, as well as any failure of tissue or blood sampling,  
296 molecular profiling and repeat biopsies.

297 Turnaround time for molecular results for liquid and tumour tissue biopsy, time to treatment  
298 initiation, treatment received and outcomes including tumour response, progression-free and  
299 overall survival will be collected.

300 Patients will be asked to complete the EQ-5D-5L at baseline and at 3 months to assess  
301 quality of life. Patients may complete the EQ-5D-5L survey by phone or by mail if they do not  
302 have a routine (in person) doctor's visit scheduled. Patients that are unable to complete the  
303 EQ-5D-5L (literacy, physical issues, unavailable translation) are still eligible to participate.

304 Patient visits and procedures during the diagnostic work up will be collected. Costs of both  
305 diagnostic strategies will be captured using time in motion studies, direct costs from UHN and  
306 list costs as appropriate. These will be presented as a cost-consequence analysis of liquid  
307 biopsy vs. standard of care tissue biopsy and molecular profiling.

308

## 309 **4. SELECTION OF SUBJECTS**

310 Patients referred to the Lung RAMP program will be eligible if they are deemed to have  
311 advanced lung carcinoma by imaging. These patients (all cases) are currently discussed at  
312 the weekly Lung RAMP Multidisciplinary Cancer Conference (MCC) that includes thoracic  
313 surgery, interventional respirology, radiology, radiation and medical oncology representatives.  
314 Patients reviewed at MCC who meet the inclusion criteria will be approached to participate in  
315 the study as part of their ongoing diagnostic work up.

### 316 **4.1. Inclusion Criteria:**

317 Patients referred to the Lung RAMP program with radiologic evidence of advanced disease  
318 (incurable stage III or IV) will be eligible, if the following criteria are met:

- 319 1. MCC or study team confirms radiologic (clinical) evidence of advanced, incurable  
320 lung cancer;
- 321 2. Measurable disease (presumed malignant) by RECIST 1.1;
- 322 3. Age  $\geq 18$  years;
- 323 4. Ability to provide written informed consent;
- 324 5. Diagnostic biopsy and molecular profiling ordered or planned. Patients remain  
325 eligible even if biopsy or tumour testing later fails or is deemed not feasible.

### 326 **4.2. Exclusion Criteria:**

- 327 1. Pregnancy;
- 328 2. Concurrent active malignancy except for localized non-melanomatous skin cancer  
329 or non-invasive cervical cancer. Any previous cancer (excluding NSCLC) must

have been treated more than 2 years prior to study entry with no current evidence of active disease.

## **5. STUDY PROCEDURES AND OBSERVATIONS**

### **5.1. Schedule of Procedures and Observations**

All participants must provide written, signed, informed consent using the latest approved version of the Institutional Research Ethics Board informed consent form (ICF). A copy of the signed ICF will be given to the subject. The original will be kept on file in study records. Study overview is shown in Figure 4.

### **5.2. Screening Period**

The following procedures and assessments must be completed prior to pre-study assessment:

- MCC review and confirmation of eligibility
- Informed Consent

### **5.3. Pre-Study Period (can be same day as screening)**

- Blood collection into 4 Streck cell preservation tubes (40 mL)
- Baseline quality of life assessment using the EQ-5D-5L

### **5.4. Study Period**

Patients will proceed with standard of care diagnostic work up, imaging, tumour biopsy and tumour tissue molecular profiling through Lung RAMP. There may be some variability in timing of scans and tests.

- Repeat quality of life assessment will be administered at 3 months (12 weeks +/- 4 weeks) from study blood collection using the EQ-5D-5L
- Molecular profiling results from both tumour and ctDNA will be recorded
- Patients will be treated as per standard of care based on tissue and/or blood genotyping results
- Time to treatment initiation and patient visits/procedures will be recorded

